Taking into consideration exam scores as well as interview scores, we anticipate that 70 candidates will be accepted to the program. 50 will be included in the full intervention group, and 20 candidates will be selected for the soft skills component of the program; they are known as the partial intervention group. An additional 10 candidates will be selected from the pool of applicants who narrowly miss being accepted into the program and will be assigned to the control group, which will have no intervention.

The interview guidelines and rubric will be designed after evaluating the applicant pool to ensure a tailored and contextually appropriate selection process. The rubric will assess multiple criteria, including applicants' clarity and coherence of responses, which reflects their ability to clearly and logically express their thoughts during the interview. It will also evaluate motivation and commitment, particularly their interest in the New Dimensions program and future career goals. Relevance of experience or academic background will be considered to assess how well the applicant's previous experience aligns with the skills taught in the program. Socioeconomic need will be another key criterion, with priority given to those from underprivileged or at-risk communities. Time management skills, especially the ability to balance the program with other commitments, will also be evaluated. Lastly, the rubric will assess the potential for success, offering a holistic evaluation based on overall interview performance. The rubric will remain flexible to allow adjustments depending on the overall strength of the applicant pool; for instance, if the pool is stronger than expected, the criteria will become more stringent to ensure fair and meaningful differentiation between candidates.

The allocation of 50, 20, and 10 participants to the full intervention, partial intervention, and control groups, respectively, considers the program's merit-based selection and its practical constraints. It balances the desire to provide comprehensive training to a larger cohort against the anticipated lower engagement from the partial intervention group, who receive less training, and the control group, who may be less motivated due to not being selected for any training. This structure aims to ensure an effective assessment of the program's impact while navigating the limitations of participant availability and commitment.

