### Statistical plan

6.3

Descriptive statistics will be used to summarize the demographic characteristics of the study population and examine the distribution of outcome variables. Continuous variables will be summarized as means and standard deviations or medians and interquartile ranges depending on their distribution. Categorical variables will be summarized as frequencies and percentages.

To assess the effectiveness of the *New Dimensions program*, we employ a quasi-experimental design with two intervention groups and one control group. The two intervention groups will be compared to the control group to evaluate the impact of the program on employability and well-being outcomes.

To test for differences in baseline characteristics between the intervention and control groups, we used *t*-tests for continuous variables and chi-square tests for categorical variables. To examine changes in the outcome variables over time, we plan to employ linear mixed-effects regression models. Models will include fixed effects for group (full/partial/control), time (baseline/endline/12-month), and the group × time interaction (primary estimand), with random intercepts for participants. These models will allow us to account for the within-subject correlation of repeated measurements over time and adjust for potential confounders, such as age and educational level. We will additionally adjust for city, baseline employment status, and motivation score (tertiles). This will help to control for variations in motivation that could impact outcomes, thereby reducing the risk of false positives. By adjusting for motivation, we aim to ensure that the observed effects are more likely to be attributable to the intervention itself rather than pre-existing differences between groups.

Missing data will be handled using complete case analysis when the proportion of missing data is low and assumed to be missing completely at random (MCAR). For cases where missingness is more substantial, we will implement inverse probability weighting (IPW) to adjust for potential differences between participants who remain in the study and those lost to follow-up. Descriptive comparisons between retained and lost participants will also be performed to assess systematic differences that could influence the results.

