All statistical tests will be two-sided, with a significance threshold of *p* < 0.05. Missing data will be addressed using Multiple Imputation by Chained Equations (MICE) under MAR assumptions, with sensitivity analyses including complete-case and IPW approaches. Given the exploratory sample size (*n* = 80), we will emphasize precision of estimates (95% confidence intervals) rather than sole reliance on *p*-values, and will apply small-sample robust standard errors where appropriate. All analyses will be conducted in Stata 19.0.

To prevent undisclosed flexibility in our analysis pipeline, as mentioned before, we have predefined all primary and secondary outcomes and will adhere strictly to the outlined statistical methods. Outcome-neutral conditions are established by employing validated instruments known to avoid floor or ceiling effects. Given that the study is exploratory due to funding and resource constraints, no formal power calculation was performed. Therefore, some analyses, particularly those involving subgroup comparisons (e.g., differences between full and partial intervention groups), should be considered exploratory. Assumptions for our analyses include approximate normality of continuous variables and that data are missing at random (MAR), both of which will be examined through diagnostic and sensitivity checks. Missing data will be addressed using Multiple Imputation by Chained Equations (MICE) under MAR assumptions, and effect sizes with 95% confidence intervals will be reported and compared across imputed and complete-case approaches. Robustness will be evaluated by repeating models both with and without adjustment for baseline motivation scores. Finally, to address potential selection bias from the non-random assignment of participants to the full-intervention group, we will perform propensity-score inverse probability of treatment weighting (IPTW) sensitivity analyses based on age, education, city, baseline employment status, and motivation score.

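### The checks named in section 6.3 cannot examine the missing-at-random assumption as the plan says they will; they inform on MCAR and on the imputation model only

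*Protocol article*

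**What the plan says.** All of this stands in section 6.3 (Statistical plan) of the protocol article.

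- Two assumptions are listed, approximate normality and "that data are missing at random (MAR), both of which will be examined through diagnostic and sensitivity checks".
- Missing data are to be handled by multiple imputation (MICE) under MAR, "with sensitivity analyses including complete-case and IPW approaches".
- The one comparison spelled out is that "effect sizes with 95% confidence intervals will be reported and compared across imputed and complete-case approaches".
- An earlier paragraph of the same section reserves complete-case analysis for small amounts of missing data taken to be MCAR. For larger amounts it uses "inverse probability weighting (IPW) to adjust for potential differences between participants who remain in the study and those lost to follow-up".
- It adds: "Descriptive comparisons between retained and lost participants will also be performed to assess systematic differences that could influence the results".

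The two paragraphs differ on which method leads. That does not affect this point, because the set of methods is the same either way. No analysis that departs from MAR is named. The section also commits the authors to keep strictly to the methods it outlines.

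**The concern.** The plan makes a positive claim, that MAR will be examined, and places beside it methods that cannot do so. A reader of the results may then take similar estimates across methods as evidence for MAR, or different estimates as evidence against it. Neither inference is sound.

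The stakes come from the small control group. Section 5.8 puts 10 women in it, so each is 10 percentage points of the control employment rate. If three had no 12-month answer (an assumption), the control rate in all 10 could lie anywhere from k/10 to (k+3)/10, where k is the number of responders in work. That is a 30-point span, and MAR alone decides where in it the estimate falls. Employment and income are primary outcomes, and either could plausibly affect whether a woman answers a survey a year later.

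**Working it through.** **Step 1. What each named check assumes**

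| Check | Rests on |
|---|---|
| MICE | MAR, as the plan states |
| Complete case | MCAR, as the plan states |
| IPW for loss to follow-up | MAR given the variables in the weight model |
| Retained versus lost | Observed data only; can cast doubt on MCAR |

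MAR says that, given group and earlier visits, the 12-month outcome has the same distribution in non-responders as in responders. The non-responders' distribution is never observed. Shifting their values by any constant fits the observed data equally well, so no comparison built on observed data can separate MAR from a departure from it (MNAR).

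**Step 2. Simulation inputs**

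The plan gives no figure to reproduce. From the document: 50 in the full arm and 10 controls (section 5.8). Everything else is assumed.

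- Baseline b is standard normal and g is 1 for the full arm, 0 for control.
- Endline: y1 = 0.6b + 0.15g + 0.8e1.
- 12 months: y2 = 0.3b + 0.5y1 + 0.425g + 0.7e2.
- True difference: 0.425 + 0.5 × 0.15 = 0.50. The within-arm variance of y2 is 0.09 + 0.25 + 2 × 0.3 × 0.5 × 0.6 + 0.49 = 1.01, so units are close to SDs.
- Baseline and endline are always observed; 28% to 31% of y2 is missing.
- Analysis: regression of y2 on group and baseline, a simplification of the planned mixed model. Imputation uses group, baseline and endline. IPW uses the same plus endline × group.

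Logit of the probability that y2 is missing, with s = +1 in the full arm and −1 in control:

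- A, MCAR: −0.85
- B, MAR: −1 − b
- C, MAR: −1 − 1.5·s·y1
- D, MNAR: −1 − 1.5·s·(part of y2 not predicted by b, y1 and g)
- E, MNAR: −1 − 1.5·s·y2

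**Step 3. Large samples (2,500 per arm, 40 runs)**

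| Case | No loss | Complete case | IPW | Imputation | Complete case − imputation | Imputation − no loss |
|---|---|---|---|---|---|---|
| A | 0.504 | 0.501 | 0.502 | 0.502 | −0.001 | −0.002 |
| B | 0.502 | 0.502 | 0.503 | 0.502 | 0.000 | 0.000 |
| C | 0.500 | 0.738 | 0.505 | 0.500 | 0.238 | 0.000 |
| D | 0.507 | 0.877 | 0.878 | 0.879 | −0.002 | 0.372 |
| E | 0.502 | 0.928 | 0.808 | 0.836 | 0.092 | 0.334 |

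In C, MAR holds and the spelled-out comparison disagrees by 0.24. In D, MAR fails and all three methods agree, with a shared bias of 0.37. In E, MAR fails and the methods spread by 0.928 − 0.808 = 0.12, all of them biased.

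**Step 4. The trial's size (50 versus 10, 1,500 runs)**

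| Case | MAR holds? | Complete case and imputation differ by more than 0.2 | Bias of imputation |
|---|---|---|---|
| A | yes | 9% | 0.004 |
| C | yes | 53% | 0.008 |
| D | no | 9% | 0.374 |
| E | no | 19% | 0.332 |

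A visible gap is most frequent in a case where MAR is true. It is no more frequent in D, where MAR fails, than in A, where data are missing completely at random.

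**The case against.** Several things can fairly be said for the plan.

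- The sentence on MAR does not itself name the comparisons, and the list of sensitivity analyses is introduced as open. A separate analysis plan, not shown, may hold an MNAR analysis. So the absence of one is not the point here. What stands is the statement in 6.3 that MAR will be examined, made beside checks that cannot do it and with a promise to keep to the outlined methods.
- The study is described as exploratory, stresses intervals over p-values, and has a retention protocol (section 5.6) and consented employment verification (section 5.7.1). These lower the stakes. Verification is there to triangulate self-reports, though, and depends on consent; it is not presented as a source for missing answers.
- The simulated mechanisms run in opposite directions in the two arms. They were chosen to show what can happen and nothing in the document makes them likely.

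Two stronger readings are tempting and not supported. A reader might infer that the methods agree whatever the truth, so that the check can never fail. Cases C and E refute this. Nor does 6.3 set a rule by which agreement counts as support; it says only that results will be reported and compared, and its sentence on robustness concerns adjustment for motivation score. A reader might also take section 5.2 on "the control group, who may be less motivated due to not being selected for any training" as evidence of MNAR. That remark explains the group sizes and suggests at most that loss differs by arm. Arm is observed, so such loss is compatible with MAR.

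**Conclusion.** The point holds in this limited form: the named checks are uninformative about MAR. That follows from the assumptions of the methods and needs no simulation. The simulation illustrates the size: a shared bias of about 0.37 SD with full agreement under one MNAR mechanism, and a 0.24 SD disagreement under one mechanism where MAR holds. These sizes rest on about 30% missing, the chosen strengths and directions, a continuous outcome and a simplified model. The 0.24 gap also depends on complete case meaning that women without a 12-month value are dropped altogether. It is a correction worth making to the stated claim, and it does not show that the trial's data will be MNAR or its estimates biased.

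**What to change.** In section 6.3:

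1. Replace the statement that MAR will be examined by one saying that MAR cannot be tested from the observed data and is assumed for the main analysis.
2. Keep complete case, IPW and the retained-versus-lost comparison, described as checks on MCAR and on the imputation model.
3. Add one sensitivity analysis for employment and income at 12 months. After imputation, shift the imputed values by a fixed delta, separately by arm, over a range set in advance (for example 0 to ±0.5 SD of income, and odds of employment from halved to doubled). Report the smallest shift that changes whether the interval for the primary contrast includes no effect.
4. Describe robustness to missing data only against that tipping point.

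The cost is wording and a short loop over imputations already planned in Stata; no new data are needed. The downside is a little more to report, and the stated robustness may become less favourable.

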### Assignment of interventions

5.10

The full intervention group, comprising both hard and soft skills training, will be selected from the full pool of applicants based on economic need, academic, and motivational merit by a team of four reviewers. Thus, owing to the nature of this application process, the intervention for the full group will not be randomly assigned. A pool of applicants who narrowly misses being selected for the full intervention group will be created. Participants from the soft skills-only (partial intervention) and control groups will be randomly selected using Microsoft Excel's random-number generator function. Random selection will be conducted within strata defined by city (Quito/Guayaquil), baseline employment status (employed vs. not), and motivation score tertiles to minimize imbalance. Excel RAND() will be used to generate random numbers separately within each stratum, followed by rank-ordering and assignment.

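### The planned IPTW and the covariates named for the mixed model leave out most of the scores that decide entry to the full arm, so they may not remove selection bias from full-arm contrasts

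*Protocol article*

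**What the plan says.** Section 5.10 states that "the intervention for the full group will not be randomly assigned" and that this arm "will be selected from the full pool of applicants based on economic need, academic, and motivational merit by a team of four reviewers". Section 5.2 describes the admission scores: "Taking into consideration exam scores as well as interview scores, we anticipate that 70 candidates will be accepted to the program". On the interview rubric it adds: "Socioeconomic need will be another key criterion, with priority given to those from underprivileged or at-risk communities". Controls come from applicants who narrowly miss admission.

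Section 6.3 makes the group × time interaction the primary estimand of a linear mixed model with participant random intercepts. The model is to "adjust for potential confounders, such as age and educational level", and then also for city, baseline employment status and motivation score in tertiles. The same section plans propensity-score weighting "to address potential selection bias from the non-random assignment of participants to the full-intervention group", specified as "inverse probability of treatment weighting (IPTW) sensitivity analyses based on age, education, city, baseline employment status, and motivation score".

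The scores exist as data. Section 6.1 has applicants sit the exam and interviewers score the responses, and section 6.2 has candidates' scores stored.

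**The concern.** A propensity score removes confounding only by the variables in it. Here the assignment process is known and its inputs are recorded, yet most of those inputs are missing from the analysis written to correct for it. Education and baseline employment are at best proxies for academic merit and need.

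Full-versus-control serves the primary objective. Performance on a mathematics exam and in an interview could well predict who later gains a job or a higher income, with or without the training. If so, part of an observed full-arm advantage would reflect who was admitted, while the report could state that selection bias had been addressed.

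**Working it through.** **1. Selection criteria against planned covariates**

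| Criterion for the full arm | Where stated | In IPTW list | Named for mixed model |
|---|---|---|---|
| Exam score | 5.2 | no | no |
| Interview score | 5.2 | no | no |
| Economic need | 5.2, 5.10 | no | no |
| Academic merit | 5.10 | education, as proxy | education, as proxy |
| Motivation | 5.2, 5.10 | yes | yes, in tertiles |

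The IPTW list is closed. The mixed-model list opens with examples, so it is formally open, but motivation is the only selection score it names.

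**2. What the primary estimand already removes**

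Write the outcome of person i at time t as group + time + group × time + b·Xᵢ + uᵢ + error. In the change from baseline, b·Xᵢ and uᵢ cancel. Two things follow:
- A score that shifts the outcome by a constant amount at every visit does not bias the group × time contrast. Bias needs a score that predicts change.
- A baseline score entered only as a main effect leaves that contrast essentially unchanged. To adjust it, the score must interact with time or enter a model for change.

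**3. Illustrative size**

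The protocol gives no bias or effect figure to reproduce. Only the arm sizes come from it (50 full, 10 control). Everything else in this simulation is an assumption:
- 200 applicants; selection index = exam + interview + need + motivation + noise; the top 50 form the full arm; 10 controls are drawn at random from the next 60.
- True effect 0. Each SD of exam and of interview score adds g to the change, in units of the residual SD of change. Need affects selection but not change.
- Correlation of each score with motivation 0, 0.3 or 0.6. Motivation is continuous, which favours the plan.
- 300 runs per setting, so Monte Carlo error is about 0.02 to 0.03 (for example 0.33/√300 = 0.019 and 0.50/√300 = 0.029).

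Mean spurious full-versus-control difference (SD), range over the three correlations:

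| g | Unadjusted change | Change model, plan's covariates | IPTW, plan's covariates | Change model, scores added | IPTW, scores added |
|---|---|---|---|---|---|
| 0 | −0.03 to 0.04 | −0.04 to 0.04 | −0.02 to 0.05 | −0.03 to 0.06 | −0.02 to 0.03 |
| 0.1 | 0.11 to 0.16 | 0.13 to 0.16 | 0.12 to 0.18 | −0.03 to 0.02 | 0.09 to 0.14 |
| 0.2 | 0.20 to 0.31 | 0.20 to 0.24 | 0.26 to 0.29 | −0.03 to 0.01 | 0.17 to 0.27 |
| 0.3 | 0.27 to 0.38 | 0.25 to 0.38 | 0.34 to 0.48 | −0.06 to 0.01 | 0.20 to 0.34 |

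The planned IPTW removes essentially none of the bias. Regression on the plan's covariates helps only when the omitted scores correlate strongly with motivation (0.6). That column already lets the covariates act on change; as main effects only, they would leave roughly the unadjusted column. For g above 0, adding the scores raises the empirical SE of the change model from about 0.33–0.42 to 0.40–0.50 SD.

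**The case against.** Much of the other side's case stands.

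- **The estimand cancels stable differences.** True, and it limits the point to scores that predict change. A reader might infer a firmer figure: a gap of 0.8 to 1.2 SD on the selection score, times a correlation of 0.3 with the outcome, gives 0.24 to 0.36 SD; against an SE of √(1/50 + 1/10) = 0.346, a 0.3 SD bias would put the false-positive rate near 14%. The documents do not support this. The correlation is with the outcome level, and the gap rests on an assumed 100 to 200 finalists. The SE is for a single time point. For a change it is 0.346 × √(2(1 − r)): 0.346 at within-person correlation r = 0.5, 0.41 at 0.3 and 0.27 at 0.7.
- **The sign is not known.** Priority for need could push income and employment the opposite way to exam merit. The simulation gave need no effect on change, so it does not settle the net direction.
- **Motivation may be a partial proxy**, since the interview rubric also rates it. This stands in part, as the 0.6 setting shows. A reader might also see harm in the stage-one motivation cut-off, but every arm passed it, so it creates no difference between arms. The tertiles match the stratification in section 5.10 and are secondary.
- **The study is exploratory, openly quasi-experimental, and IPTW is only a sensitivity analysis.** All true. But the mixed model names no further selection score, and the Limitations section does not name confounding by selection.
- **The remedy buys little accuracy.** At g = 0.2 the root mean squared error of the change model is √(0.239² + 0.399²) = 0.47 before and √(0.032² + 0.469²) = 0.47 after, at zero correlation with motivation. What improves is the centring of the interval, not its width.

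**Conclusion.** The omission is a matter of text and holds. The weighting meant to deal with non-random entry to the full arm, and the covariates named for the mixed model, include motivation but not the exam score, interview score or any measure of need. They may therefore leave selection bias in contrasts with the full arm, wherever those scores predict change in employment or income. That is plausible but not shown.

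Under the stated assumptions about 0.12 to 0.48 SD remains, and nothing if the scores do not predict change. These figures illustrate a range; they do not estimate this trial's bias. It would go too far to say that the plan cannot correct the bias at all or that the full-arm effect is bound to be inflated: the documents fix neither the size nor the sign. Partial-versus-control is unaffected, taking sections 5.3 and 5.10 at their word that both groups are drawn at random from one near-miss pool.

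**What to change.** - **Outcome model.** Add the recorded exam score, the interview composite and one measure of economic need (the personal-situation score or application-time socioeconomic data), each with its interaction with time, or fit an equivalent baseline-adjusted change model. Main effects alone do not alter the group × time estimand.
- **IPTW.** Add the same scores to the covariate list, report overlap and balance on them, and restrict to the common range or use overlap weights if overlap is poor. The weighting should not stand alone: with the scores added it still left 0.09 to 0.34 SD in the simulation, because selection on them leaves little overlap with 10 controls.
- **Wording of section 6.3.** Describe contrasts with the full arm as observational with possible residual selection bias, instead of presenting the weighting as the answer to it.

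The analysis changes need wording only, since the scores are already to be recorded. The price is wider intervals (SE about 0.40–0.50 instead of 0.33–0.42 SD in the simulation) and fragile weights, because several more covariates must be supported by 10 controls.
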